## Exploratory Efficacy Analyses

The exploratory efficacy analysis will evaluate differences in neural activity (EEG data) across two comparisons:

1. Cue Exposure Condition: Neural activity during the Conscious phase will be compared to the Unconscious phase, regardless of emotional valence.
2. Emotional Valence: Neural activity for Negative images will be compared to Positive images, regardless of cue exposure condition.

To minimize individual variability, EEG segments will be paired within participants:

- For cue exposure comparisons, the i-th EEG segment from the Conscious phase will be paired with the corresponding i-th segment from the Unconscious phase.
- For emotional valence comparisons, EEG segments from Negative and Positive image groups will be paired for the same participant.

Statistical significance will be assessed using two-sided Wilcoxon signed-rank tests for each set of paired comparisons. To support these comparisons, descriptive statistics (median value of power spectral density for each channel and frequency band, W statistics, p-values) will be calculated. The summary statistics and results will be reported in accordance with Section 9 of this SAP.

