## Endpoints

(ICH E9; 2.2.2)

1. Primary Endpoint

- Endpoint: Short-term memory suppression (METEOR scores).
- Definition: Memory suppression will be assessed using METEOR scores, a measure of semantic similarity reflecting accurate and context-rich recall.
- Time Point: Day 1 (immediately post-intervention).
- Comparisons:
- Cue exposure conditions: Conscious vs Control, Unconscious vs Control.
- Subgroup analysis: Positive vs Negative emotional valence.
- Hypothesis:
- Total Image Group: Conscious < Control, Unconscious < Control (one-tailed t-test).
- Negative Image Group: Conscious < Control, Unconscious < Control (one-tailed t-test).
- Positive Image Group: Conscious < Control, Unconscious < Control (one-tailed t-test).

2. Secondary Endpoints

- Endpoint 1: Long-term memory suppression (METEOR scores over time).
- Definition: Assessment of METEOR scores on Day 2 (24 hours post-intervention) and Day 4 (72 hours post-intervention) to evaluate memory suppression persistence.
- Time Points: Day 1, Day 2, Day 4.
- Analysis: Repeated paired t-tests (Conscious vs Control, Unconscious vs Control).
- Endpoint 2: Group differences in memory performance trajectories.
- Definition: Evaluation of memory decline over time using Difference-in-Differences (DID) analysis, adjusted for covariates such as: feedback Cycle Times (duration of self-feedback process during the learning phase), and frequency of Image Repetition (number of image viewings during the learning phase).
- Purpose: To supplement time-specific t-test comparisons and better understand group differences in forgetting trajectories.
- Endpoint 3: Emotional valence-based comparisons.
- Definition: Paired two-tailed t-tests comparing METEOR scores across valence conditions at each time point:
- Negative Treatment vs Positive Treatment
- Negative Conscious vs Positive Conscious.
- Negative Unconscious vs Positive Unconscious.
- Negative Conscious vs Positive Unconscious.
- Negative Unconscious vs Positive Conscious.

3. Exploratory Endpoints

- Endpoint: EEG-based neural activity analysis.
- Definition: Neural activity will be compared across cue exposure conditions and emotional valence groups using EEG power spectrum density.
- Frequency Bands: Alpha, beta, theta, delta, and gamma.
- Comparisons:
- Cue Exposure: Conscious vs Unconscious phases.
- Emotional Valence: Negative vs Positive image groups.
- Statistical Method: Two-tailed Wilcoxon signed-rank test for paired comparisons.

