**Detailed Description of Variables**

1. Feedback cycle times (Learning phase) :

- Definition: The time participants take to process and respond to feedback during the learning phase
- Numeric Range: Recorded in seconds
- Exclusion Rule: Outliers defined as those outside the interquartile range (IQR) will be excluded from analysis.

1. The frequency of Image repetition (Learning phase):

- Definition: The number of times participants repeatedly viewed images during the learning phase.

1. METEOR Score (Memory Performance):

- Definition: Semantic similarity score reflecting accurate and context-rich recall of cue-target pairs.
- Numeric Range: continuous variables with no predefined range. Higher scores indicate greater semantic recall accuracy.
- Handling Missing Data: Missing scores will not be imputed.

1. Gist Score (Memory Performance):

- Definition: Percentage of core narrative elements (Gist items) accurately recollected from each scene, reflecting participants’ ability to recall essential story components.
- Numeric Range: expressed as percentages, with a theoretical range of 0% (no Gist items recollected) to 100% (all Gist items recollected).
- Handling Missing Data: Missing scores will not be imputed.

1. EEG Data (Neural Activity):

- Definition: Neural activity recorded during the gaming phase, segmented into 2-second epochs for analysis.
- Exclusion Rule: EEG data with significant artifacts (e.g., noise, poor electrode contact) will be excluded.

1. Adverse Event Monitoring:

- Definition: Documentation of any unexpected physiological or psychological effects during the study period.

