## Missing Data

(ICH E3; 9.7.1, 11.4.2.2. ICH E9;5.3. EMA Guideline on Missing Data in Confirmatory Clinical Trials)

Missing data will be quantified as a percentage for each variable, including METEOR scores, Gist scores, and EEG epochs.

- **Patterns of Missingness:** Missing data will be categorized as permanent, transient, or monotonous to identify potential causes.
- **Handling Missing Data:**
  - Missing METEOR and Gist scores will not be imputed; analyses will use available data (complete case analysis).
  - Missing EEG epochs due to artifacts will be excluded from analysis.

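### The EEG analysis pairs 2-second segments and never reduces them to one value per participant; if segment pairs are the Wilcoxon unit, as the text most plainly reads, p-values are too small whenever a participant's pairs are positively correlated

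*SAP*

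**What the plan says.** SAP section 5.3 (Study Variables, EEG Data) defines the data as "Neural activity recorded during the gaming phase, segmented into 2-second epochs for analysis". Section 9.3 (Exploratory Efficacy Analyses) then gives the general rule: "To minimize individual variability, EEG segments will be paired within participants".

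- For Conscious against Unconscious, "the i-th EEG segment from the Conscious phase will be paired with the corresponding i-th segment from the Unconscious phase".
- For Negative against Positive, "EEG segments from Negative and Positive image groups will be paired for the same participant". No rule says which segment is matched with which.
- The test: "Statistical significance will be assessed using two-sided Wilcoxon signed-rank tests for each set of paired comparisons". Section 4.2 (Endpoints) names the same test, "Two-tailed Wilcoxon signed-rank test for paired comparisons", without a unit.
- The output: "median value of power spectral density for each channel and frequency band, W statistics, p-values".

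Section 7.4 (Missing Data) adds that "Missing EEG epochs due to artifacts will be excluded from analysis". In section 16 (Listing of Tables, Listings and Figures), each of the two EEG comparisons is one row for the Full Analysis population, reporting PSD, W and p. Nowhere does the SAP average segments within a participant before testing, or specify a mixed model, a clustered test or a participant-level permutation.

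**The concern.** The signed-rank test treats the differences it is given as independent. Pairing within a participant removes that person's overall EEG level. It does not remove the person's own Conscious-minus-Unconscious difference, which all of their pairs share. Neighbouring segments may also be serially correlated. If all pairs enter one test, the number of units is participants times pairs, and segments are counted as though they were separate people.

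The index matching is a second, distinct weakness. The SAP names no event or stimulus that links the i-th segment of one phase to the i-th segment of the other. For valence it gives no matching rule at all, so two analysts could follow the text and obtain different values of W.

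What is at stake is objective 4 in section 4.1, the neural correlates. The EEG tables and the brain plot are the only neural evidence planned. Channels and bands could be reported as significant because of how the units were counted, with no effect in the population of participants.

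**Working it through.** The SAP states no power, sample size or error rate for the EEG test, so there is no planned figure to reproduce.

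**Inputs from the SAP.** Segments last 2 seconds (5.3). There are 150 planned participants (6), fewer after EEG exclusions by a number not given. There are 18 game sessions (10.1). The test is a two-sided Wilcoxon signed-rank test (9.3).

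**Assumptions.**
- Nominal level 0.05 two-sided. Section 9 states 5% for the t-tests; none is stated for EEG.
- m = 9 to 100 pairs per participant. With non-overlapping segments this is 9 × 2 = 18 s to 100 × 2 = 200 s of usable recording per condition.
- ICC of the pair differences within a participant, 0 to 0.10.

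**Number of units.** With 150 participants, pooling gives 150 × 18 = 2,700 pairs at m = 18 and 150 × 60 = 9,000 at m = 60. One difference per participant gives at most 150.

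**Formula.** Design effect: DEFF = 1 + (m − 1) × ICC. True error: 2 × (1 − Φ(1.96 / √DEFF)).

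Example, m = 100 and ICC 0.05: DEFF = 1 + 99 × 0.05 = 5.95; √5.95 = 2.44; 1.96 / 2.44 = 0.80; true error 0.42.

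| Pairs per participant | ICC 0 | ICC 0.01 | ICC 0.05 | ICC 0.10 |
|---|---|---|---|---|
| 9 | 5% | 5.9% | 9.8% | 14.4% |
| 18 | 5% | 7.0% | 15.0% | 23.3% |
| 60 | 5% | 12.0% | 32.4% | 45.6% |
| 100 | 5% | 16.5% | 42.2% | 55.3% |

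**Simulation check** (1,000 runs per setting, actual Wilcoxon test). At N = 150 and ICC 0.10, the pooled-segment test rejected in 21.8% of runs at m = 18 and 45.1% at m = 60, close to the formula. At ICC 0.05 and m = 60 it gave 29.4%, a little below the formula's 32.4%. More participants do not help: N = 50, m = 60, ICC 0.10 gave 44.0%. With one median difference per participant, the error was 3.4% to 6.6% in all 20 settings, which is 5% within simulation error.

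**Effect on a reported p-value.** A pooled-segment p of 0.001 has z = 3.29. Dividing by √DEFF gives:
- m = 18, ICC 0.05: 3.29 / √1.85 = 2.42, p about 0.016
- m = 18, ICC 0.10: 3.29 / √2.70 = 2.00, p about 0.045
- m = 60, ICC 0.10: 3.29 / √6.90 = 1.25, p about 0.21

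**Effect of the matching.** One data set was simulated with N = 150, m = 18, unit within-participant variance in each condition, and a participant-specific condition difference with SD 0.3. The ICC of the pair differences is 0.09 / (1 + 1 + 0.09) = 0.043. The same segments were randomly re-paired within participants 200 times. The pooled p ranged from 0.0008 to 0.021, with a median of 0.0044. The data did not change, only the matching.

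**The case against.** Several points on the other side have force.

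*The unit is not stated.* This stands as a limit. A reader might infer that the SAP names the segment as the unit; it does not. The inference rests on the pairing rule, the missing aggregation step, and the single table row per comparison. If separate tests within each participant were meant, the SAP has no rule for combining them into the W and p of that row, so section 9.3 would need correction on that reading too.

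*The size is assumed.* This also stands. A reader might conclude that the p-values are bound to be far too small. The SAP gives neither the segment count nor the ICC, and with few pairs and an ICC near zero the inflation is slight or absent. The calculation varies only a participant-level ICC; serial correlation is not modelled.

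*Index pairing does not itself inflate error.* Correct: at ICC 0 the rate stays at 5%. The inflation comes from clustering. Arbitrary matching costs reproducibility.

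*Artifact removal need not shift the index.* Dropping the whole pair would preserve it, and the SAP is silent, so misalignment is a possibility only. A protocol not shown here might also describe some alignment across sessions; the objection to the matching is that section 9.3 states no basis for it.

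*The brain maps.* A reader might suppose that they will display p-values. Sections 11 and 16 list median differences, W and power spectrum density for the plot; p appears only in the tables.

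*Multiplicity.* Testing each channel and band in two comparisons without adjustment is a separate matter. The number of channels is not given, and unadjusted p-values in a labelled exploratory analysis are defensible.

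*The analysis is exploratory.* True, and this limits the severity. It does not excuse a test applied to dependent units.

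**Conclusion.** The point holds in a conditional form. Followed as most plainly read, section 9.3 applies a test that requires independent differences to clustered segment pairs. Its p-values are too small whenever the within-participant correlation of those differences is positive. The size ranges from none at ICC 0, through about 6% to 7% true error at ICC 0.01 with 9 to 18 pairs, to 42% to 55% at ICC 0.05 to 0.10 with 100 pairs. It rests on assumed ICCs and segment counts, an assumed 5% two-sided level, and an inferred unit. The lack of a stated basis for the index matching, and of any rule for valence, needs no assumption.

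A reader might infer that the trial's efficacy conclusion is compromised. It is not: the primary and secondary METEOR analyses (9.1 and 9.2) do not use the EEG test. This is a should-fix.

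**What to change.** Replace the segment pairing in section 9.3. For each participant, channel and band, take the median (or the mean of log) PSD over all valid epochs in the Conscious phase, and likewise in the Unconscious phase. Do the same for Negative and Positive images. Run the two-sided Wilcoxon signed-rank test on the one paired difference per participant, and state in sections 9.3 and 4.2 that the participant is the unit. No segment then has to be matched with another, so the matching problem disappears and an unequal number of surviving epochs does not prevent the comparison.

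False discovery rate control over channels and bands is an optional addition.

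The cost is a few sentences in the SAP and a small code change, with no new data. The price is that p-values will generally be less favourable, because at most 150 differences enter each test rather than several thousand.

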## Derived variables

1. Timepoint-Specific METEOR/Gist Score Comparisons

- Definition: A derived variable representing the differences in METEOR and Gist scores between groups (e.g., Control vs Conscious, Control vs Unconscious) at each assessment timepoint: Day 1, Day 2, and Day 4.

This variable allows for the evaluation of whether group differences persist, diminish, or change over time.

2. Timepoint-Specific METEOR/Gist Score Change

- Definition: A derived variable representing the within-group change in METEOR and Gist scores across the three assessment timepoints (Day 1, Day 2, and Day 4).

This variable is used to measure the progression or decline of memory performance over time for each group.

3. EEG-Based Neural Activity Comparisons

- Definition: A derived variable representing the differences in EEG power spectrum density across the following conditions:
- Cue Exposure Condition: Conscious vs Unconscious phases.
- Emotional Valence: Negative vs Positive image categories.

This variable enables the identification of significant neural activity differences associated with exposure conditions and emotional valence.

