# Efficacy Analyses

The efficacy variables in this study will be summarized to evaluate the effects of exposure condition (Control, Conscious, Unconscious), emotional valence (Positive, Negative), and test timepoint (Day 1, Day 2, Day 4).

For each combination of exposure condition, valence, and timepoint, the continuous efficacy variables, METEOR scores, will be summarized using descriptive statistics. Specifically, the mean and standard deviation (SD) will be calculated to provide an overview of performance across the different treatment groups. To formally compare METEOR scores between groups, paired t-tests will be conducted at a 5% significance level.

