**Exploratory Endpoints**

- Topographical Brain Plots: Visualizations of power spectrum density will be created to display the median differences in each EEG channel across the following frequency bands: alpha, beta, theta, delta, and gamma.
  - Comparisons will include:
- Conscious vs Unconscious
- Negative vs Positive

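### The EEG plan tests significance over channels, five bands and two contrasts with no multiplicity control, yet uses the tests to identify significant neural differences

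*SAP*

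**What the plan says.** SAP Section 9.3 "will evaluate differences in neural activity (EEG data) across two comparisons": Conscious against Unconscious phases, and Negative against Positive images. It then states: "Statistical significance will be assessed using two-sided Wilcoxon signed-rank tests for each set of paired comparisons". The supporting output is described as follows: "descriptive statistics (median value of power spectral density for each channel and frequency band, W statistics, p-values) will be calculated".

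Section 4.2 lists the bands: "Alpha, beta, theta, delta, and gamma". Section 11 plans topographical plots to "display the median differences in each EEG channel across the following frequency bands". In the listing in Section 16, Figure 6.4 is a topographical plot that carries W statistics, and the two EEG tables (both numbered 6.1) report power spectrum density, W and p, with no adjusted p-value.

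Section 4.3 gives the purpose of the EEG variable: "This variable enables the identification of significant neural activity differences associated with exposure conditions and emotional valence".

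The SAP contains no multiplicity adjustment, no cluster or permutation method, and no channel or band chosen in advance for these tests. It also gives no significance level for them. The 5% level appears only for the METEOR comparisons, where "paired t-tests will be conducted at a 5% significance level" (Section 9; repeated in Section 9.1).

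**The concern.** A topographical plot of W needs one W per channel, so the plan appears to produce one test for every channel, band and contrast. With that many tests, some p-values will fall below any conventional cut-off even if neither contrast affects the EEG. The SAP offers no criterion that takes the number of tests into account, and its wording invites the reader to treat small p-values as identified differences.

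What is at stake is Objective 4, the neural correlates of memory suppression, which rests on this analysis alone. Neighbouring channels share signal, so false positives tend to fall together and can look like a regional effect on a scalp map.

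**Working it through.** The SAP states no error rate for the EEG tests, so there is no figure to reproduce.

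**Inputs from the SAP**
- Contrasts: 2 (Section 9.3).
- Bands: 5 (Section 4.2).
- Test: two-sided Wilcoxon signed-rank (Section 9.3).
- Adjustment: none stated.

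**Assumptions, because the SAP is silent**
- Level: 5% per test, carried over from the METEOR tests.
- Channels: K, shown from 1 to 32.
- Correlation between tests: from none to very strong.
- Each test is valid by itself, with one paired value per participant.

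**Number of tests.** K channels × 5 bands × 2 contrasts = 10K.

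**Independent cells.** P(at least one p < 0.05 with no true difference) = 1 − 0.95^(10K):
- K=1: 1 − 0.95^10 = 40.1%
- K=2: 1 − 0.95^20 = 64.2%
- K=4: 1 − 0.95^40 = 87.1%
- K=8: 1 − 0.95^80 = 98.4%

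**Correlated cells.** This is a simulation of null studies with correlated normal test statistics. All channels share one correlation, all bands share another, and the two contrasts are independent. Repeat runs agreed to within about one percentage point.

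| K | Tests | Independent | 0.8 / 0.5 | 0.9 / 0.8 | 0.95 / 0.9 | Expected false-positive cells |
|---|---|---|---|---|---|---|
| 1 | 10 | 40% | 33% | 24% | 19% | 0.5 |
| 2 | 20 | 64% | 47% | 32% | 24% | 1 |
| 4 | 40 | 87% | 61% | 39% | 28% | 2 |
| 8 | 80 | 98% | 75% | 47% | 33% | 4 |
| 32 | 320 | >99.9% | 91% | 61% | 41% | 16 |

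Column labels give channel correlation / band correlation. The last column is 10K × 0.05 = K/2, which does not depend on the correlation.

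**Check with actual Wilcoxon tests.** With 150 participants and correlations 0.8 / 0.5, 400 null studies gave 73% (K=8) and 91% (K=32), in line with the table.

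**Stricter level.** At 1% per test with independent cells, 1 − 0.99^(10K) gives 9.6% (K=1), 55% (K=8) and 96% (K=32).

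**The remedy on the same null studies.** Benjamini-Hochberg at 5% over all 10K p-values as one family makes at least one call in about 2% to 5% of null studies. With a separate family for each contrast the rate is about double, roughly 4% to 10%, in line with 1 − 0.95² = 9.75% for two independent families.

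**The case against.** Four objections deserve an answer.

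- **The SAP writes no rule that one small p-value is an effect.** A reader might infer that the plan declares a neural difference whenever any cell is below 0.05, and so would report one in most studies with no effect. The text does not support that. It states neither such a rule nor a level for the EEG tests. The rate also depends on channel count and correlation: it is below 50% for one channel, and stays below 50% at 32 channels if the correlations are 0.95 and 0.9. What remains is that the SAP speaks of assessing significance and gives no criterion suited to the number of tests.

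- **The tests might be one per contrast.** In Section 9.3, the words on channel and band could attach only to the median power. Two tests would give 1 − 0.95² = 9.75%. This reading is possible but hard to square with Figure 6.4, which maps W over the scalp.

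- **The endpoint is exploratory.** This stands as a limit on importance, since nothing primary or secondary depends on it. W and p are also tabulated, so readers can see that there are many tests. It does not remove the problem, because a purely descriptive analysis would not claim to identify significant differences.

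- **An adjustment does not repair invalid p-values.** This stands. Section 9.3 pairs the i-th segments within participants and does not say that they are reduced to one value per participant. In an illustrative simulation with segments pooled (150 participants, 100 segments each, intraclass correlation 0.05), a single nominal 5% test rejected about 45% of the time with no effect. Benjamini-Hochberg on such p-values would not deliver the control claimed for it.

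**Conclusion.** The point holds in conditional form. On the most natural reading, the SAP runs 10K unadjusted Wilcoxon tests and uses them to identify significant EEG differences, with no stated level and no multiplicity control.

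Even the most favourable setting in the table, 19% (one channel, correlations 0.95 and 0.9), is nearly four times a nominal 5%. A map drawn by channel implies more than one channel. How far above that the true rate lies cannot be settled from the SAP, because channel count, level and correlation are missing. All figures assume 5% per test and a valid participant-level test.

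The sponsor should correct this before analysis. It bears on Objective 4 only.

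**What to change.** **Preferred.** In Section 9.3, replace the significance sentence with text to this effect:

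*For each participant, channel and band, segment power is reduced to one paired value per comparison before testing. The Wilcoxon p-values over all channels, the five bands and both comparisons form one family. Benjamini-Hochberg adjusted p-values are reported beside the raw ones. A channel-band difference is called significant, and marked in Figure 6.4, only if its adjusted p-value is below 0.05.*

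State the number of channels, name the participant-level summary (for example the median over valid segments), and add an adjusted p-value column to both tables numbered 6.1. A participant-level sign-flip permutation using the maximum statistic over channels, bands and both comparisons is an acceptable alternative.

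**Lighter option.** Remove the significance wording from Sections 4.3 and 9.3 and label the EEG p-values nominal and descriptive.

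**Cost.** No new data are needed. The adjustment itself is a short step in code. If the current code tests pooled segments, the power values must first be reduced to participant level and the tests rerun. The downside is that isolated weak differences lose the label of significance, though their raw p-values remain visible.
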